## Monitoring subject compliance

No monitoring of subject compliance is necessary as all treatment is administered during surgery within hours of randomization during which the patient is anesthetized.

## WOMEN OF CHILDBEARING POTENTIAL (WOCBP)

Males being included in the trial that have WOCBP partners are required to use a condom from the time of treatment and 90 days postoperatively. This period may be extended in the case of adjuvant therapy. For non-pregnant WOCBP partner, contraception is recommended.

WOCBP being included in the trial shall have a highly effective negative pregnancy test performed as part of the inclusion criteria. The following highly effective birth control (<1% failure rate) should be in use prior to study inclusion and continue for 6 months after surgery (extended another 6 months in the case of adjuvant therapy administration).

1: Combined (estrogen and progestogen containing) hormonal contraception associated with inhibition of ovulation

o oral

o intravaginal

o transdermal

2: Progestogen-only hormonal contraception associated with inhibition of ovulation

o oral

o injectable

o implantable

3: Intrauterine device (IUD)

4: Intrauterine hormone-releasing system ( IUS)

5: Bilateral tubal occlusion

6: Vasectomised partner

7: Sexual abstinence

# TREATMENT OF SUBJECTS

## Treatment administration

A previous dose-titration study from France has shown that 400 mg/m^2^ of both oxaliplatin and irinotecan HIPEC were the maximum tolerated dosages. However, after some further use, the doses have been around 360mg/m^2^ in clinical routine due, primarily, to neutropenia [11]. In this trial, this slightly lower dosage will be kept (even though neutropenia appears to be a positive factor for disease-free survival without risk of increase in other postoperative morbidity), in order to be able to have some margin upon which to dose-titrate the 5-FU 24-hour EPIC.

At the discretion of the surgeon (e.g. co-morbidity), the surgeon/oncologist is allowed to decide on a dose reduction; either give the full study dose – 100% of planned dosing, or 25% dose reduction – which is a 25% reduction of all chemotherapeutic treatments during the HIPEC procedure.

The HIPEC may be administered with any HIPEC administration device that is approved for this purpose. The administration may be done with the open or closed abdominal technique. The targeted temperature is 41-42 degrees Celsius. The chemotherapy perfusion time is 30 min and the perfusion rate is targeted to 1 liter per min, but may be adjusted as needed to keep the HIPEC treatment going and keep the temperature stabile in the abdomen. A minimum of 2 temperature probes are required in the abdomen to monitor the target temperature. Gastrointestinal reconstruction is optionally performed prior to or after the HIPEC procedure.

The EPIC procedure may commence once the abdomen is completely shut which includes completing skin closure and stoma suturing. Administration is described below in Arm B. At least two drains must be left in the abdomen with one in the upper abdomen and one in the pelvic region which are required in order to administer EPIC. The drains must be sutured to the skin and should not allow fluid leakage. A slightly diagonal trajectory through the abdominal wall with purse string sutures is an appropriate method of drain placement (other methods are allowed as long as no fluid leakage occurs).

Arm A (HIPEC) Standard treatment (normal dose and 1 dose level reduction)

- Oxaliplatin – 460 mg/m^2^ (HIPEC) – 25% dose reduction 350 mg/m^2^
- 5-FU – 400 mg/m^2^ IV bolus (Intraop) – 25% dose reduction 300 mg/m^2^
- Calcium folinate 60 mg/m^2^ IV (Intraop)
- Granulocyte colony stimulating factor given postoperative only as needed when the leukocyte count falls below normal range.

Arm B (HIPEC + EPIC) Experimental treatment (normal dose and 1 dose level reduction)

- Oxaliplatin – 360 mg/m^2^ (HIPEC) – 25% dose reduction 270 mg/m^2^
- Irinotecan – 360 mg/m^2^ (HIPEC) – 25% dose reduction 270 mg/m^2^
- 5-FU – 400 mg/m^2^ IV bolus (Intraop) - 25% dose reduction 300 mg/m^2^
- Calcium folinate – 60 mg/m^2^ IV (Intraop)
- 5-FU – 250-850 mg/m^2^ IP 24-hour dwell in 400ml of 9% saline solution (End of op) (25% dose reduction 190-640 mg/m^2^)
  - The EPIC treatment is only 1 day and is administered after the abdomen is completely sutured in the operating theatre. The dose will be divided equally into 2 injections á 200ml each through two abdominal drains. The drains may be flushed with 20ml saline solution so that the chemotherapy is not lingering in the drain catheter. Afterwards, all drains are clamped for 16 hours. They are then opened in order to drain the abdominal cavity postoperatively.
- Granulocyte colony stimulating factor (G-CSF – e.g. filgrastim 5µg/kg/day) administered prophylactically on postoperative day 4 to 8 (5 days). If the neutrophil count is under normal range after 5 days of prophylactic treatment, the treatment may continue until the count is normalized, as clinically indicated. If leucocytosis occurs, the prophylactic treatment can be terminated earlier than after 5 days.

G-CSF may be administered as needed before or after the prophylactic period if an early or late neutropenia is detected.

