## Study assessments and procedures

### Dose titration

A single-arm dose titration trial (Table 1). Sample size: minimum 15 patients (3 patients per dose level) – maximum 30 (6 patients per dose level) patients.

Table 1. Dose escalation of 5-FU 24-hour EPIC for each titration level and concomitant treatment where irinotecan is also an investigational drug (the other drugs are non-investigational and given to both groups in the randomized part of the trial).

| Level | Non-investigational  Oxaliplatin | **Investigational**  **Irinotecan** | **Investigational**  **5-FU**  **24-hour EPIC** | Non-investigational  5-FU  bolus | Non-investigational  Calcium folinate |
| --- | --- | --- | --- | --- | --- |
| -1 | 360 mg/m^2^ | **360 mg/m^2^** | **250 mg/m^2^** | 400 mg/m^2^ | 60mg/m^2^ |
| 0 | 360 mg/m^2^ | **360 mg/m^2^** | **400 mg/m^2^** | 400 mg/m^2^ | 60mg/m^2^ |
| 1 | 360 mg/m^2^ | **360 mg/m^2^** | **550 mg/m^2^** | 400 mg/m^2^ | 60mg/m^2^ |
| 2 | 360 mg/m^2^ | **360 mg/m^2^** | **700 mg/m^2^** | 400 mg/m^2^ | 60mg/m^2^ |
| 3 | 360 mg/m^2^ | **360 mg/m^2^** | **850 mg/m^2^** | 400 mg/m^2^ | 60mg/m^2^ |

Endpoint is Clavien-Dindo morbidity classification 3b-5 (Table 2). All patients will be reviewed at each of the dose levels by the DMC prior to allowing the next group of patients to advance to the following level. The toxicity follow-up is 30 days if no incidents occur. If the postoperative rehabilitation is slower or incidents occur, the follow-up period may be extended to by the site Principal Investigator or Co-investigator.

If none or one of the first three patients at a dose level has a grade 3b-4b the DMC will review the data and permit the start of the next level. If more than one patient experiences a grade 3b-4b another three patients will be included at the same dose level before the DMC will review the data. A frequency of 3b-4b morbidity in ≤1 of 3 or ≤2 of 6 patients may result in a recommendation by the DMC to proceed to the next dose level. A higher frequency of grade 3b-4b means the maximum tolerated dose (MTD) has been passed, and the dosage used in the efficacy study will be the nearest underlying dose level. Any grade 5 event pauses all inclusion for review. Depending on cause, the trial may continue after DMC review.

Table 2. Clavien-Dindo classification.

| Grades | Definition |
| --- | --- |

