## Description of investigational products

Irinotecan – 360mg/m^2^: This investigational drug will be procured in a syringe by the hospital pharmacy for a one-time administration. It will be injected into the HIPEC perfusate circulating in the hyperthermic pump via the injection site. It will be injected together with oxaliplatin that is a non-investigational drug that all patients will receive irrespective of arm.

5-fluorouracil – Maximum tolerated dose of 1-day EPIC to be determined: This investigational drug dose will be divided into two separate syringes. It will be injected through two of the remaining passive abdominal drains. After injection, the drain will be cleared from chemotherapy with a saline solution injection. The drains will be clamped. The estimated peritoneal clearance is 8-10 hours. The clamps need to be closed 16 hours. They are then opened for drainage of fluid collections to occur according to our clinical routine for abdominal drains in HIPEC.

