## Storage and handling

Both drugs are actively used every week in the medical oncology outpatient clinics in all four participating centers in routine oncology treatment. Thus, each center hospital has a constant turnover of the investigational medicinal product (IMPs) fluorouracil and irinotecan. Due to the common use of these drugs, there is little need for specific IMP drug oversight. Each pharmacy will store, handle, dilute and prepare the drugs according to the specifics as described in the published marketing drug IMP brochure (see FASS.se).

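### Section 10.1 gives the carrier for intraperitoneal 5-FU as 9% saline, ten times physiological strength and almost certainly meant as 0.9%, and nothing else in the protocol corrects it

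*Protocol*

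**What the plan says.** Section 10.1 (Treatment administration) first describes the EPIC procedure in general terms and then refers the reader on: "Administration is described below in Arm B". The Arm B list is therefore where the protocol fixes how EPIC is given. Its 5-FU item reads "IP 24-hour dwell in 400ml of 9% saline solution (End of op". It continues: "The dose will be divided equally into 2 injections á 200ml each through two abdominal drains", and then "Afterwards, all drains are clamped for 16 hours".

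Other places touch on the same preparation:

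- The synopsis and section 8.1 repeat the two 200 ml injections but name no diluent.
- The flush in section 10.1 is described as "The drains may be flushed with 20ml saline solution so that the chemotherapy is not lingering in the drain catheter", with no strength.
- Section 10.2 says "After injection, the drain will be cleared from chemotherapy with a saline solution injection", again with no strength.
- Section 10.4 says "Each pharmacy will store, handle, dilute and prepare the drugs according to the specifics as described in the published marketing drug IMP brochure". It gives no concentration and does not mention intraperitoneal use.

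**The concern.** The carrier is part of the experimental treatment, and the protocol states its strength once, at ten times the physiological value. If 9% were intended, a rationale would be expected, because a strongly hypertonic fluid would be left in the abdomen straight after cytoreductive surgery. There is none. The equivalence of 0.9% and 9 mg/ml offers a simple explanation for a slip.

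The stakes are conditional on someone preparing the dose as printed. Two consequences would then follow.

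- **Patient safety.** A tenfold salt load would sit behind clamped drains. The laboratory values that section 8.3 collects (haemoglobin, CRP, white cells, neutrophils, platelets, albumin, creatinine, ALT) do not include sodium, so the trial's own record would not show it.
- **Dose finding.** The carrier volume is the same at every 5-FU level, so the load would be present from 250 mg/m² upwards. The titration rule in section 8.2.1 counts events by grade, without an exception for cause: "A higher frequency of grade 3b-4b means the maximum tolerated dose (MTD) has been passed". Harm from the carrier could therefore be counted against 5-FU when the maximum tolerated dose is set.

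**Working it through.** **Inputs**

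- Carrier: 9% saline, 400 ml given as 2 × 200 ml (section 10.1, Arm B).
- 5-FU stock: 50 mg/ml (section 10.3).
- 5-FU dose range: 250 to 850 mg/m² (section 8.2.1, Table 1).
- Molar mass of sodium chloride: 58.44 g/mol; two ions per formula unit. Physiological saline is 0.9% w/v. Both are general knowledge.
- Body surface: 1.6 to 2.0 m². This is an assumption, needed only for the second reading below.

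**Reading 1: the 400 ml is all diluent**

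Mass = volume × concentration; amount = mass / 58.44; theoretical osmolarity = 2 × amount / volume.

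| | 9% (as printed) | 0.9% |
| --- | --- | --- |
| Concentration | 90 g/l | 9 g/l |
| NaCl in 400 ml | 400 × 0.09 = 36 g | 400 × 0.009 = 3.6 g |
| Sodium | 36 / 58.44 = 0.616 mol (616 mmol) | 3.6 / 58.44 = 0.0616 mol (62 mmol) |
| Osmolarity | 2 × 0.616 / 0.4 = 3.08 Osm/l (3,080 mOsm/l) | 2 × 0.0616 / 0.4 = 0.308 Osm/l (308 mOsm/l) |

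**Reading 2: the 400 ml is the total, drug solution included**

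Drug volume = dose × body surface / 50; the rest is diluent.

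- Smallest drug volume: 250 × 1.6 / 50 = 8 ml, leaving 392 ml. NaCl = 392 × 0.09 = 35.3 g, or 604 mmol sodium.
- Largest drug volume: 850 × 2.0 / 50 = 34 ml, leaving 366 ml. NaCl = 366 × 0.09 = 32.9 g, or 564 mmol sodium.
- At 0.9% the same volumes give 3.3 to 3.5 g, or 56 to 60 mmol.

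The two readings differ by at most 36 − 32.9 = 3.1 g, so the conclusion does not depend on which is meant. The ratio of printed to physiological strength is ten in both.

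**Is the rest of the line sound?** The 25% reductions printed with it are right: 250 × 0.75 = 187.5, given as 190, and 850 × 0.75 = 637.5, given as 640. The error is confined to the saline strength.

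**Does any other section settle the strength?** No. The synopsis and section 8.1 name no diluent, the flush sentences in 10.1 and 10.2 give no concentration, and 10.4 points to an outside source. The 9% stands alone and uncorrected.

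**The case against.** The strongest reply is that this is a missing zero with probably no effect on any patient. Dilution belongs to hospital pharmacies, and section 10.4 tells them to follow the marketed-product information. The drugs are in weekly use at the participating centres, and a pharmacist would very likely use ordinary saline. The salt loads above describe something that will probably not happen. The route to a distorted maximum tolerated dose needs several further steps: literal preparation, carrier toxicity reaching grade 3b-4b, enough such events to cross the threshold, and no one recognising the cause. The data monitoring committee reviews every dose level and investigators judge causality (section 12.2). Finally, a lost character in reading the PDF cannot be wholly excluded.

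Most of this stands as a limit on weight. Literal preparation is unlikely, and the dose-finding consequence is a possibility for which the protocol gives no evidence either way. The absence of a cause exception is a feature of the titration rule itself and does not come from the saline figure. The text around the number is intact, so a reading fault is a small doubt that a look at the source page resolves.

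What does not stand is that section 10.4 cures the error. It names no strength, does not address intraperitoneal dilution and does not say that it overrides 10.1. The product information is not in the protocol, so what it says about a carrier cannot be checked here. Sites listed as pending in Denmark and Norway would also work from the protocol text, and they should not have to rely on Swedish routine to spot the slip.

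**Conclusion.** The concern holds: the carrier strength in section 10.1 is wrong as written. It is a fault in the treatment specification and should be fixed, although actual harm is unlikely.

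Taken literally, the instruction means 36 g of sodium chloride, about 616 mmol sodium at about 3,080 mOsm/l. If the 400 ml includes the drug and body surface is 1.6 to 2.0 m², it means 32.9 to 35.3 g. Each figure is ten times its value at 0.9%. The instruction applies to the phase I patients (15 to 30 if all five levels are completed) and to the 163 planned for Arm B. Those are the numbers it covers and do not predict how many would be harmed. If pharmacies use 0.9% regardless, no patient is affected and only the document is wrong.

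That 0.9% was intended is an inference from the missing rationale and the tenfold ratio. Only the sponsor can confirm it.

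**What to change.** Confirm the intended strength. If it is 0.9%, change the Arm B item in section 10.1 to *400 ml of 0.9% (9 mg/ml) sodium chloride*, and make the pharmacy preparation instruction under section 10.4 say the same. While the line is open, it would help to state whether 400 ml is the diluent alone or the total volume including the drug. If a hypertonic carrier is really intended, say so in 10.1 and justify it.

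The cost is a one-line protocol correction and a matching pharmacy instruction. Endpoint, sample size and analysis are untouched.

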| Number of subjects (planned):  Dose escalation study: min 15 and max 30 patients - Number of patients is based on toxicity observed.  Efficacy study: 326 patients. Interim analysis is done after 140 patients are included | | |
| Diagnosis:  Colorectal cancer | | |
| Inclusion criteria:   1. Provision of written informed consent prior to any study specific procedures. 2. ECOG Performance Status Score 0,1 or 2 alternatively Karnofsky 60-100 3. Adequate kidney, liver, bone marrow function according to laboratory tests 4. For females of childbearing potential, a negative pregnancy test must be documented 5. ≥ 18 years old and <75 years old 6. Colorectal cancer with peritoneal metastases +/- liver metastases (maximum 3) 7. All patients deemed eligible for CRS and HIPEC according to clinical routine management during a HIPEC multidisciplinary board at each respective hospital can be included. | | |
| Exclusion criteria:   1. Previous severe toxicity/allergic reactions to systemic chemotherapy agents oxaliplatin or irinotecan or 5-fluorouracil 2. Unable to tolerate intensified HIPEC treatment due to comorbidity 3. Metastasis other than peritoneum or liver 4. Complex liver-perenchymal sparing surgery or hemihepatectomy procedures are to be excluded. 5. Previous CRS or HIPEC 6. Pregnant or lactating (nursing) women 7. Active infections requiring antibiotics 8. Active liver disease with positive serology for active hepatitis B, C, or known HIV 9. Concurrent administration of any cancer therapy other than planned study treatment within 4 weeks prior to and up to 4 weeks after study treatment 10. Incomplete cytoreduction defined as completeness of cytoreduction score 1-3 11. Histopathology of other origin than colorectal cancer | | |
| Investigational product, dosage and mode of administration:  Injection of irinotecan 360 mg/m^2^ and 5-fluorouracil 24-hr EPIC 250-850 mg/m^2^ in combination with Oxaliplatin 360 mg/m^2^ and an intraoperational IV of 5-fluorouracil bolus 400 mg/m^2^ with calcium folinate 60mg/m^2^.  The EPIC treatment is given after the abdomen is completely sutured in the operating theatre. The dose will be divided equally into 2 injections á 200ml each through two abdominal drains. | | |
| Duration of treatment:  24 hours | | |
| Active control, dosage and mode of administration:  Injection of oxaliplatin 460 mg/m^2^ and an intraoperational IV of 5-fluorouracil 400 mg/m^2^, and calcium folinate 60 mg/m^2^ | | |

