# ENDPOINTS

## Primary Endpoint

### Phase I

- Maximum tolerated dose of 5-FU 24-hour EPIC. Possible toxicity will be reported as Adverse Events.

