# STUDY DESIGN

## Study outline

A dose titration study and a combined superiority registry-based open-label randomized control trial is planned to answer the trial objectives. The study will be registry-based to allow simpler and more comprehensive follow-up. Patients with colorectal cancer will be treated with cytoreductive surgery (CRS) together with either standard oxaliplatin HIPEC (the control for the efficacy study) or oxaliplatin/irinotecan HIPEC in combination with 5-FU 24-hour EPIC. The 5-FU will be administered postoperatively when the abdomen is completely sutured. The drug is divided equally into 2 injections of 200 ml each and injected through two abdominal drains that are clamped for 16hours.

For dose escalation, the titration groups (á 3 or 6 patients) are followed for 30 days postoperatively after which the Data Monitoring Committee (DMC) will determine whether or not to increase the 5-FU dose for the following group of patients.

To study efficacy, randomization is performed intraoperatively. The patient is followed up postoperatively for a total of 3 years for the secondary endpoints which may be extended by the study committee to 5 years. Since the trial is registry based, the long-term follow-up does not require separate eCRF evaluations. These evaluations can be automatically retrieved from the registry – both recurrence data, quality of life, and morbidity data. Some specific eCRF evaluations will be integrated as a separate study part of the HIPEC registry, such as inclusion/exclusion criteria and adverse event reporting (including SUSAR reporting).

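### Protocol 10.1 specifies 9% saline, ten times isotonic, as the diluent for the 5-FU EPIC instillate; this is very likely a slip for 0.9% and should be corrected

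*Protocol*

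**What the plan says.** Section 10.1 (Treatment administration) refers the reader to its Arm B list for how EPIC is given. In that list the intraperitoneal 5-FU entry, covering the whole range of 250 to 850 mg/m², reads "IP 24-hour dwell in 400ml of 9% saline solution (End of op". The line therefore serves the phase I dose levels as well as the randomized experimental arm. The 400 ml is given as two injections of 200 ml through two drains. A 20 ml saline flush is also allowed, with no concentration stated.

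On preparation, section 10.4 (Storage and handling) says: "Each pharmacy will store, handle, dilute and prepare the drugs according to the specifics as described in the published marketing drug IMP brochure".

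On duration, the synopsis has "Duration of treatment: 24 hours". The sub-bullet directly under the dose line in 10.1 says: "Afterwards, all drains are clamped for 16 hours. They are then opened in order to drain the abdominal cavity postoperatively". Section 10.2 says: "The estimated peritoneal clearance is 8-10 hours. The clamps need to be closed 16 hours", and adds that the drains are then opened. Section 8.1 describes the drug as "injected through two abdominal drains that are clamped for 16hours". The regimen is named by its day elsewhere too: the phase I endpoint in 7.1.1 is the "Maximum tolerated dose of 5-FU 24-hour EPIC", and 10.2 has "Maximum tolerated dose of 1-day EPIC to be determined".

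**The concern.** The diluent is part of the preparation instruction for an investigational drug, in the place to which the protocol itself sends the reader. Nine per cent saline is ten times isotonic. Nothing in the background, the justification of the route or the product description explains why a strongly hypertonic carrier would be wanted. Nor can a reader correct the figure from the document, because no other section gives a saline concentration.

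If the line were followed literally, a large salt load would be put into the abdomen straight after cytoreductive surgery and held there behind clamped drains. That is a safety matter for the patient. It is not a question of statistical validity.

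The same line also describes the dwell as 24 hours although the drains are clamped for 16. That is a secondary wording point.

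**Working it through.** **Inputs.** Volume 400 ml and concentration 9% come from the Arm B dose line in 10.1. The molar mass of NaCl is 58.44 g/mol. Full dissociation into two ions is assumed (ideal osmolarity).

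**Other figures on the line, as a check.** 2 × 200 ml = 400 ml, as stated. The 25% dose reduction gives 0.75 × 250 = 187.5 (stated 190) and 0.75 × 850 = 637.5 (stated 640). Both are right after rounding, so the diluent looks like an isolated slip.

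**Salt content.** Mass = concentration (g/ml) × volume. Osmolarity = 2 × molarity.

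| | 9% as written | 0.9% |
|---|---|---|
| NaCl in 400 ml | 0.09 × 400 = 36 g | 0.009 × 400 = 3.6 g |
| Sodium | 36 / 58.44 = 0.616 mol (616 mmol) | 3.6 / 58.44 = 0.0616 mol (62 mmol) |
| Molarity | 0.616 / 0.4 = 1.54 mol/L | 0.0616 / 0.4 = 0.154 mol/L |
| Osmolarity | 2 × 1.54 = 3.08 Osm/L (3,080 mOsm/L) | 2 × 0.154 = 0.308 Osm/L (308 mOsm/L) |

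The ratio is 10 and the excess is 36 − 3.6 = 32.4 g of NaCl. This treats all 400 ml as diluent. If 400 ml is the final volume, the drug displaces some of it: at the top dose and the 50 mg/ml strength in 10.3, 850 / 50 = 17 ml per m² of body surface, or 17 × 0.09 = 1.53 g of salt per m². The ten-fold ratio is unchanged.

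**Likely origin.** 0.9% is 0.9 g per 100 ml, which is 9 mg/ml. Either a dropped decimal or a confusion of the two notations would produce the printed 9%.

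**Dwell wording, side by side.**
- 10.1 dose line: 24-hour dwell. Synopsis: treatment duration 24 hours.
- 8.1: clamped 16 hours, with opening not mentioned.
- 10.1 sub-bullet: clamped 16 hours, then opened.
- 10.2: clamped 16 hours, then opened; estimated clearance 8–10 hours.

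The label exceeds the clamp by 24 − 16 = 8 hours. The clamp is already 16/10 = 1.6 to 16/8 = 2.0 times the stated clearance.

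**The case against.** The strongest defence is that the slip is self-evident and already guarded against. Section 10.4 sends dilution and preparation to hospital pharmacies that handle these drugs routinely, under the published product information. For harm to follow, a pharmacy would have to make up an unusual ten-fold hypertonic diluent without querying it, and nothing in the protocol suggests that this would happen. That argument stands as far as likelihood goes. It does not remove the error: 10.4 names no concentration and does not say that it overrides 10.1, which is the specific instruction. Section 10.4 also speaks of four centres, whereas the synopsis and 13.3 list Aarhus and Oslo as pending, so the text may reach pharmacies new to the trial.

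It could also be said that a decimal point was lost in the electronic text. This cannot be fully excluded, but other decimals in the document are intact (0.35, 0.40 and 0.15 in the interim analysis section of 13.2.1; 0.05 in 13.4).

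Three stronger readings are tempting and are not supported:
- A reader might infer that patients will receive hypertonic saline. The document shows a wrong figure, not its use.
- A reader might infer that the 24-hour wording changes drug exposure or undermines the MTD or the arm comparison. Every procedural sentence gives 16 hours, that time applies alike to every dose level and to phase III, and it exceeds the stated clearance. The 24-hour and 1-day terms serve as the regimen's name, setting this single instillation apart from the 5-day EPIC used elsewhere. The phrase is loose, but it is not an error on a par with the diluent.
- A reader might infer that all three clamp statements have the drains opened at 16 hours. Section 8.1 gives the clamp time only; 10.1 and 10.2 add the opening.

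**Conclusion.** The diluent point holds. Section 10.1 states 9% saline where 0.9% is very likely meant, a ten-fold difference (36 g against 3.6 g of NaCl in 400 ml; about 3,080 against 308 mOsm/L). The intended 0.9% is an inference from the absence of any rationale, since no section states it. The osmolarities assume ideal full dissociation. They describe what the text specifies and do not predict what patients would receive.

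The severity is that of a minor erratum. It deserves correction because it sits in an operative dosing instruction and because literal use, though unlikely, would be harmful. It is a drafting error and not a design choice. It has no bearing on the endpoint, randomization, sample size, interim rule or analysis.

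The dwell wording is a real but minor inconsistency, and no consequence is claimed for it.

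**What to change.** Confirm the diluent in use with the participating pharmacies, then amend the Arm B dose line in 10.1 to 0.9% saline (9 mg/ml).

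In the same amendment, replace the 24-hour dwell on that line with wording that the drains are clamped for 16 hours and then opened, and align the synopsis entry on treatment duration with it. The regimen's name can stay, provided it is defined once as a single instillation with a 16-hour clamp.

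The cost is one pharmacy query and a wording amendment. It needs no new data field, patients or procedures.
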